## Abstract

**Background:**

The global prevalence of infertility is 9%, with male factors potentially accounting for 40% to 60% of cases. Conventional treatments can be ineffective, invasive, costly, and linked to adverse effects and high risks. Previous studies have shown that, Chinese herbal medicine (CHM) can regulate the hypothalamus-pituitary-testis axis, improve sperm abnormalities and quality, mitigate oxidative stress, and decrease DNA fragmentation index (DFI). Yet, the evidence backing the use of Chinese herbal medicine (CHM) for treating male factor infertility lacks conviction due to study design limitations, and there remains a scarcity of studies on the live birth rate following CHM treatment for male factor infertility. Here, we describe the rationale and design of a randomized waitlist-controlled trial to evaluate the effect of CHM on the live birth rate among males with infertility.

**Methods:**

This study is a single-center, randomized, waitlist-controlled study. A total of 250 couples diagnosed with male factor infertility will be enrolled in this study and then randomly allocated into two groups in a 1:1 ratio. Male participants in CHM group (treatment group) will receive CHM once a day for 3 months. Male participants in the waitlist group (control group) will not receive any treatment for 3 months. After 3 months, participants in both groups need to be followed up for another 12 months. The primary outcome will be the live birth rate; secondary outcomes include semen quality parameters, DFI and pregnancy related outcomes. Safety will also be assessed.

**Discussion:**

The purpose of this trial is to explore the effects and safety of CHM on the live birth rate among couples dealing with male factor infertility. The outcome of this trial may provide a viable treatment option for male factor infertility.

**Trial registration:**

Chinese Clinical Trial Registry: ChiCTR2200064416. Registered on 7 October 2022, https://www.chictr.org.cn.

## Background

1

Infertility is defined as the failure to achieve pregnancy after 12 months of regular unprotected sexual intercourse (1). It has been reported that the worldwide fertility rates decreased from 4.7 to 2.4 live births between 1950 and 2017 (2). Additionally, there has been a parallel decrease in sperm counts (0.70 million/ml/year) noted between 1981 and 2013 (3). The global prevalence of infertility is 9% (4), with male factors potentially accounting for 40% to 60% of cases (5). Interference in any physiological stages of spermatogenesis or ejaculation can result in male infertility.

Although the conventional treatments such as medication, surgery, intrauterine insemination, and intracytoplasmic sperm injection have assisted numerous men with fertility issues in achieving clinical pregnancies (6–9). However, these treatments sometimes can be ineffective, invasive, costly or linked to adverse effects and high risks (10, 11). Therefore, it is essential to find a safe, convenient and effective method to treat male factor infertility.

Chinese herbal medicine (CHM), as an significant component of traditional Chinese medicine (TCM), has long been utilized to treat infertility in both women and men in China (12). The holism, together with syndrome differentiation and treatment, are the essence and the basic characteristics of TCM. Applying this theory to the treatment of male factor infertility has shown promising outcomes. According to TCM theory, kidney storing essence and plays a vital role in reproduction. Domestic studies have shown that kidney supplementing CHM can regulate the hypothalamus-pituitary-testis axis (13), regulate follicle-stimulating hormone (FSH) and luteinizing hormone levels bidirectionally (14–17), and finally improve the level of testosterone to improve semen quality. Furthermore, CHM can also prevent oxidative stress, reduce DNA fragmentation index (DFI) (18, 19), inhibit the apoptosis of germ cell (20–22), provide trace elements and vitamins (23, 24), and improve testicular microcirculation (25, 26).

However, there are some limitations in the existing clinical studies on CHM for male factor infertility, leading to insufficient evidence to be convincing. Most studies on CHM for male factor infertility are not randomized controlled trials, or do not provide detailed descriptions of random sequence generation and allocation concealment methods, and have small sample sizes. Furthermore, the lack of a unified evaluation standard for the efficacy of CHM has caused considerable heterogeneity. Therefore, well-designed randomized controlled trials are needed to acess the effectiveness of CHM in male factor infertility. Consequently, we have put forth a randomized controlled trial protocol to examine the influence of CHM on live birth rate among males with infertility.

The primary aim of this study is to access the hypothesis that CHM (treatment group) improve live birth rate more effectively than waitlist (control group) among males with infertility. Secondary objectives include the evaluation of semen quality parameters, sperm DNA fragmentation (SDF), pregnancy related outcomes, and adverse events.

## Methods

2

This protocol was developed following the guidelines of the Consolidated Standards of Reporting Trials (CONSORT) (27) and adheres to the Standard Protocol Items: Recommendations for Interventional Trials (SPIRIT) statement 2013 (28) (**Additional File 1**). The trial obtained ethical approval from the ethics committee at Foshan Fosun Chancheng Hospital in China (ethics approval no. CYIRB-LCYJ-2022113). It has been registered at Chinese Clinical Trial Registry (ChiCTR2200064416).

### Trial design

2.1

This is a single-center, randomized, waitlist-controlled clinical trial with 1:1 allocation ratio. The study will be conducted at Foshan Fosun Chancheng Hospital over a period of 24 months. All participants will be randomly allocated to receive CHM, once a day or waitlist for 3 months. After 3 months, participants in both groups will be followed up for 12 months. Investigators will screen based on the inclusion and exclusion criteria. This protocol aims to establish a well-designed randomized controlled trial to evaluate the effect of CHM for the improvement of live birth rate among males with infertility.

### Participants and enrollment

2.2

Recruiting at least 12-month infertile couples who meet the inclusion criteria and do not meet any exclusion criteria from the Department of TCM Gynecology in the Foshan Fosun Chancheng Hospital. Eligible participants will be contacted and will be asked to sign the consent form following a thorough explanation of the study’s design and comprehensive counseling (see the flow diagram in **Figure 1**).

**Figure 1 f1:**
[figure not shown]
The flow diagram of the study.

### Inclusion criteria

2.3

(1) Couples inclusion criteria (29)

1) Infertility lasting 12 months or longer (whether primary or secondary);

2) Heterosexual;

3) Living together and able to have regular intercourse.

(2) Male inclusion criteria (29)

1) Older than or equal to 18 years old;

2) At least one of the following semen parameter deviates from the normal range in the semen analysis conducted over the past 6 months:

a. Sperm concentration ≤15 Million/ml;

b. Total motility ≤40%;

c. Normal morphology ≤4%;

d. DFI >25%.

3) Agree to provide semen samples as the proposed timeline at baseline, after 3 months of treatment, and after 3 months of follow-up;

4) Agree to sign the consent form.

(3) Female inclusion criteria (29)

1) ≥18 years and ≤40 years of age with normal ovarian reserve, defined as an early follicular phase FSH ≤10 IU/L, AMH ≥1.0 ng/ml, or antral follicle count greater than 10;

2) Regular menstrual cycle (25 to 35 days). Evidence to confirm ovulation, including biphasic basal body temperatures, positive ovulation predictor test, or serum progesterone level ≥3 ng/ml;

3) Evidence of at least one patent fallopian tube (determined by hysterosalpingogram or laparoscopy). 

### Exclusion criteria

2.4

(1) Couples exclusion criteria (29, 30)

1) Previous history sterilization surgery, such as vasectomy or tubal ligation;

2) Planning to undergo *in vitro* fertilization within the next 15 months.

(2) Male exclusion criteria (29, 30)

1) Sperm concentration is less than 5 million/mL on screening semen analysis;

2) Present utilization of a medication or drug that would affect reproductive capabilities, for instance, anti-tumor and anti-epileptic medications;

3) Having taken CHM, Chinese patent medicine, or other treatments that could impact the research outcomes within the last three months;

4) Cryptorchidism or testicular dysplasia;

5) Genetic factors that have been discovered to lead to low fertility in males, including chromosomal disorders such as Y chromosome deletions;

6) Current poorly controlled chronic diseases diagnosed by a physician, such as heart disease, diabetes mellitus, hypertension, thyroid disorders, liver disease, kidney disease, or HIV/AIDS or cancer;

7) Unwilling to provide written consent for the study;

8) Patients who participated in other clinical studies requiring medication treatment.

(3) Female exclusion criteria (29, 30)

1) Diagnosed moderate or severe endometriosis;

2) Suffering from polycystic ovarian syndrome;

3) Body mass index greater than 35kg/m^2^;

4) Pregnant at present;

5) Currently suffering from serious medical illnesses such as cancer, heart disease, or cirrhosis

6) A history of receiving systemic chemotherapy or pelvic radiotherapy;

7) The medication or drug currently being used may affect reproductive function or metabolism.

### Randomization and patient allocation

2.5

The statisticians at the Data Coordination Centre (DCC) will create the study’s randomization scheme using the Clinical Trial Management Public Platform (ResMan, www.medresman.org.cn). A total of 250 couples will be randomly assigned to either the treatment group or the control group in a 1:1 ratio. In this study, the treatment group will undergo CHM treatment, while the control group will not receive any medication, thus making it unachievable for researchers and participants to be blinded to the treatment allocation.

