#### Screening visit

2.7.1

(1) Obtain signed informed consent and detailed medical history collection;(2) Semen analysis: semen analysis after 2–5 days of sexual abstinence included standard measurements, such as volume, pH, count, and motility. Semen samples will be assessed in the hospital laboratory using WHO 5.0 criteria (31) for sperm morphology. In addition, DFI will be evaluated using Sperm Chromatin Structure Analysis (SCSA) test (32);(3) Laboratory examination: including reproductive hormone, blood routine test (BRT), thyroid function, liver function, kidney function, chromosome examination of peripheral blood.

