#### Secondary outcomes

2.9.2

(1) Semen parameters

1) sperm concentration: quantity of spermatozoa per unit of volume of semen, 10^6^/mL;

2) morphology: percentage of normal morphology;

3) motility: percentage of motile (including nonprogressive motile and progressive motile);

4) DFI: evaluate using SCSA test.

(2) Conception rate

Conception will be determined by a positive serum β-hCG measurement (β-hCG >10 mIU/mL).

(3) Pregnancy rate

Pregnancy will be characterized as an intrauterine pregnancy with confirmed fetal heart motion via transvaginal ultrasound.

(4) Pregnancy loss rate

Pregnancy loss will be refers to the intrauterine pregnancy lost before 20 completed weeks of gestation.

(5) Pregnancy complications

Including pregnancy diabetes, pregnancy induced hypertension, preeclampsia/preeclampsia, premature birth, congenital malformations, perinatal death, etc.

(6) Reproductive hormone

Including total testosterone, follicle stimulating hormone, luteinizing hormone, estradiol, progesterone, and prolactin.

(7) Adverse events.

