### Data management

2.13

Upon enrollment in the study, each participant will be assigned a unique identifier, which will be utilized across all data records to maintain participant confidentiality. Participant data will be managed using paper case record forms (CRF) and a web-based electronic database (ResMan). Following the collection of original participant documents, they will be transferred to the CRF. Subsequently, all data will be stored in the ResMan. Quality control of the data will be managed at two distinct levels: the investigators will be responsible for ensuring data accuracy as the initial level of control during record input into the CRF. The second level will involve regular data monitoring and validation via ResMan by DCC. Any changes to the current study protocol will be presented to the institutional review board, all trial participants, and trial researchers. Ultimately, individual participant data, excluding private information, will be available to the public within 6 months after the trial’s completion.

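### Section 2.5 rules out blinding without separating roles, although the reason it gives does not reach the semen-sample readers or a data analyst

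*Protocol article*

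**What the plan says.** The protocol article, section 2.5 (Randomization and patient allocation), gives one reason for an open trial: "the treatment group will undergo CHM treatment, while the control group will not receive any medication". From this it draws a conclusion covering two groups, "thus making it unachievable for researchers and participants to be blinded to the treatment allocation". No role within the research team is exempted.

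Three other sections bear on the point:

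- Section 2.7.1 (Screening visit) places the semen work at the trial site: "Semen samples will be assessed in the hospital laboratory using WHO 5.0 criteria (31) for sperm morphology". It adds that "DFI will be evaluated using Sperm Chromatin Structure Analysis (SCSA) test".
- Section 2.9.2 (Secondary outcomes) lists sperm concentration, morphology, motility and DFI. Morphology is defined as a percentage of normal forms, and motility as the percentage of motile sperm.
- Section 2.13 (Data management) states that "each participant will be assigned a unique identifier, which will be utilized across all data records", for confidentiality.

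No section describes masked laboratory reading or masked analysis.

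**The concern.** Without a placebo, the man taking the herbal medicine, the prescriber and the staff who see him at visits know the arm. A technician at the microscope and an analyst with a data file need not know it. Section 2.5 runs these roles together and so appears to rule out a safeguard that the design permits.

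Classifying sperm as normal involves the reader's judgement, and so does motility when it is read manually. If a reader knows or can guess the arm, a small systematic leaning could look like a semen improvement under treatment. The Background presents better semen quality as part of how the medicine works, so these results would probably be read as support for the live-birth finding. The same section faults earlier studies of this treatment for weak design.

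**Working it through.** **1. Does the stated reason cover each role?**

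| Role | Does the absence of control medication reveal the arm? |
|---|---|
| Male participant and partner | Yes |
| Prescriber, visit staff | Yes |
| Reader of a semen sample labelled with identifier and visit | No |
| Analyst given arms labelled A and B | No, if this person has no allocation list |

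The premise supports the conclusion for the first two rows only. For the third row, the means already exist in the identifier of section 2.13. For the fourth, section 2.5 has the Data Coordination Centre (DCC) statisticians creating the randomization scheme, so they cannot themselves serve as masked analysts.

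**2. Which outcomes are exposed?** Morphology is exposed, and motility if read manually. DFI by SCSA probably depends less on the reader; this is a judgement, not something the article states. Live birth (section 2.9.1) is a delivery at 20 weeks or later, which laboratory reading cannot change.

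**3. Number of men per arm.** Section 2.11 assumes live-birth rates of 2.5% and 12.5%, two-sided α of 5%, 80% power and 15% dropout, and raises 105 per group to 125. With unpooled variance:

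- n = (1.960 + 0.842)² × (0.025 × 0.975 + 0.125 × 0.875) / 0.10² = 104.98, so 105, as stated.
- 105 / 0.85 = 123.5, so 124, against 125 stated.
- Expected completers: 125 × 0.85 = 106.25, so about 106 per arm.

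**4. Illustration of the possible size.** Assume no true effect, 106 men per arm, and a reading shift of d standard deviations in favour of treatment. The test statistic is then centred at d × √(106/2) = d × 7.280 instead of zero. By the normal approximation, the chance of a two-sided P<0.05 is P(Z > 1.96 − centre), because the opposite tail is negligible.

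| Assumed shift d | Centre | Chance of P<0.05 |
|---|---|---|
| 0 | 0 | 5% (both tails) |
| 0.2 SD | 1.456 | P(Z > 0.504) = about 31% |
| 0.3 SD | 2.184 | P(Z > −0.224) = about 59% |

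The range for d is an assumption; the documents give no figure for it. The result applies to each affected parameter separately.

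**The case against.** The best defence is that researchers in section 2.5 means the site staff who deal with participants. The same section names the DCC statisticians separately, section 2.13 distinguishes investigators from the DCC, and the laboratory is not mentioned in section 2.5 at all. On that reading the statement is correct and the article is merely silent on laboratory and analyst masking, which a condensed article may leave to the full protocol, laboratory procedures or analysis plan. This reading is possible and cannot be excluded. It does not remove the point, because the sentence as printed makes an affirmative claim with no exemption, and its reason does not support that claim for every role. If the narrower meaning was intended, the correction is still to name the roles.

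A reader might infer more: that laboratory staff know the allocation, that the semen results will be biased, or that the plan excludes masking for everyone on purpose. The documents support none of these. Assessment in the hospital's laboratory does not show that readers are told the arm. The identifier used across all records is compatible with samples already arriving coded. The 31% to 59% is correct arithmetic on an assumed one-directional shift, not an expected error rate for this trial.

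For the analyst, section 2.16 already names the tests for the main comparisons, so masking adds less there than in the laboratory. The choice between parametric and rank tests, and the sensitivity analyses of section 2.12, still leave some room.

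**Conclusion.** The point holds as a cheap improvement. The blinding statement does not separate roles. Its stated reason fits participants and treating or visit staff, but not semen-sample readers or a data analyst, and the article provides for their blinding nowhere else.

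What is at stake is limited to reader-dependent secondary outcomes: morphology, and motility if manual. The live-birth comparison is not exposed to laboratory reading, and sample size, power and α are unaffected. The illustrative inflation from 5% to about 31% to 59% per affected parameter depends on readers knowing the arm, on a shift of 0.2 to 0.3 SD in one direction, on no true effect, and on 106 men per arm. The first two are not established by the documents.

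**What to change.** Reword section 2.5 so that the lack of blinding applies to participants and to treating or visit staff. Then add:

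- Semen samples reach the laboratory labelled only with the study identifier and the visit, and readers are not told the arm.
- Where the DCC has an analyst without access to the allocation list, the analysis is run on arms coded A/B until it is locked. This must not be one of the statisticians who create the randomization scheme.

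The cost is a change in labelling practice and a short paragraph of text. Masked analysis also requires a suitable person, so it is conditional on one being available. Recruitment began in November 2022, and any samples already read with knowledge of the arm cannot be re-blinded. The date of the change should therefore be recorded, so that readings before and after it can be told apart. If samples already travel coded, only the wording needs to change.

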### Intervention

2.6

Couples will receive complimentary ovulation predictor tests and guidance on the timing of intercourse throughout the study.

#### Treatment group

2.6.1

The CHM used in this study contains 21 Chinese traditional medicinal herbs (**Supplementary Table 1**). The CHM prescription protocol is grounded in traditional Chinese medical theories. Following randomization, male partners in the treatment group will begin taking CHM once daily for a duration of 3 months. After a 3-month treatment period, participants will require a 12-month follow-up.

#### Control group

2.6.2

During the study period, male partners in the control group will not receive drug intervention. After a 3-month waitlist period, participants will be followed up for 12 months.

### Study-specific visits and procedures

2.7

Male participants will be required to attend several visits, which include the screening visit, baseline visit, treatment visit, and follow-up visit. Adverse events and concomitant medications will be documented at each visit. The overview of study visits is detailed in **Table 1**.

**Table 1 T1:** Overview of study visits.

Period		Treatment				Follow-up	
Time point	Screening	basal	1m	2m	3m	1m ∼ 11m	12m
**Enrollment:**							
Eligibility screen	√						
Informed consent	√						
Allocation		√					
**Interventions:**							
Waitlist		√	√	√	√		
Chinese herbal medicine		√	√	√	√		
**Assessments:**							
Case history	√						
Vital signs	√	√	√	√	√	√	√
Anthropometric ^a^	√	√	√	√	√	√	√
Safety laboratory ^b^	√				√		√
Chromosomes of the peripheral blood	√						
Sex hormone steroids ^c^	√				√		√
Semen parameter analysis	√				√		√
Adverse event		√	√	√	√	√	√
Concomitant medications	√	√	√	√	√	√	√
Partner pregnancy test	√	√	√	√	√	√	√

^a^Anthropometric: weight, height, waist circumference, hip circumference. ^b^Safety laboratory: Blood routine test, thyroid function, renal and liver profile. ^c^Sex hormone steroids: Total testosterone, follicle stimulating hormone, luteinizing hormone, estradiol, progesterone, prolactin.

#### Screening visit

2.7.1

(1) Obtain signed informed consent and detailed medical history collection;(2) Semen analysis: semen analysis after 2–5 days of sexual abstinence included standard measurements, such as volume, pH, count, and motility. Semen samples will be assessed in the hospital laboratory using WHO 5.0 criteria (31) for sperm morphology. In addition, DFI will be evaluated using Sperm Chromatin Structure Analysis (SCSA) test (32);(3) Laboratory examination: including reproductive hormone, blood routine test (BRT), thyroid function, liver function, kidney function, chromosome examination of peripheral blood.

#### Baseline visit

2.7.2

After the screening visit, couples who meet the inclusion criteria will be assigned to the baseline visit and randomly allocated. Complete anthropometric (height, weight, hip circumference, waist circumference), vital signs measurement.

#### Treatment visit

2.7.3

During the treatment period, visits were conducted at the end of each month, including the records of anthropometric, vital signs, compliance, adverse events and concomitant medication. At the end of the third month, the male partners in both groups will measure the following parameters within 1 week:

(1) Anthropometric: height, weight, hip circumference, waist circumference;(2) Semen analysis, DFI;(3) Laboratory examination: reproductive hormone, BRT, liver function, kidney function.

